## Abstract

**Background:**

Young women exposed to a high hereditary breast and ovarian cancer (HBOC) risk are particularly vulnerable. They are ignored by health prevention measures but exposed to a stream of contradictory information (medicine, media, Internet). They may feel concerned about surgical prevention issues at a key moment of their identity construction (self, relationship, sexuality). We designed a special psychoeducational intervention to help these women cope better with these difficulties.

**Methods/design:**

The BRACAVENIR study consists of a prospective, randomized superiority phase II trial with a wait list control group. Participants are childless young female counselees (aged 18–30 years) seen at the oncogenetics department of the Centre Jean Perrin and belonging to HBOC families either with or without *BRCA* mutations. They will be invited to attend a weekend group session at a spa resort and to participate in short expert conferences and focus group activities (group sharing, Moreno role game) supervised by a psychotherapist. Two sessions separated by a 6-month delay (wait list) will enable us to evaluate the intervention’s effect by comparing questionnaire scores between the 6-month time points. The main endpoint is an increase of the Herth Hope Index by at least 1 SD. Secondary endpoints are self-esteem, anxiety trait, anxiety state, coping, and quality of life. With a one-sided α = 0.05 and β = 0.20, 12 participants will be needed by group, plus an additional 2 in anticipation of dropouts. Participants will be randomized 1:1 to the first or the second session so that the groups will be comparable.

**Discussion:**

The intent of this trial is to bridge the gap on a psychosocial level in these young women with HBOC. A particularity of the design is the use of a waiting list, which should allow for avoiding major bias. The intervention consists of a short session that could be proposed to other young counselees if successful. The results may bring complementary information to facilitate the intervention and also influence the contents of the oncogenetic consultation.

**Trial registration:**

Ethics committee CPP SUD-EST-6: IRB00008526. Registered on 18 March 2016.

ClinicalTrials.gov identifier: NCT02705924. Registered on 2 March 2016.

**Electronic supplementary material:**

The online version of this article (doi:10.1186/s13063-016-1642-4) contains supplementary material, which is available to authorized users.

## Background

Carriers of mutations favoring the development of cancer in adulthood encounter various life difficulties. In addition to an increasing cancer risk with age, many questions arise concerning the future and how to build long-term projects. Although prevention and medical screening receive great support from health institutions, most psychosocial consequences remain unanswered. Among members of cancer-prone families, some are ignored by health systems, in particular the youngest women exposed to a high risk for breast and ovarian cancer. Indeed, these women are too young to be concerned with prevention measures. However, some of them have already been confronted by a mother’s disease and experienced their mothers’ early death. This early period of their lives also makes them vulnerable as they face identity issues, the onset of romantic relationships, or questions about how to plan for procreation [1, 2].

In parallel, these young women stand in the cross fire of an abundance of contradictory information spread by the media, websites, or internet forums. The rapid evolution of medicine adds to this cacophony in terms of possible prophylactic surgery, assisted procreation, embryo selection, and gene therapies, with discordant voices between specialists, even in Western countries. Unfortunately, prophylactic interventions directly address the intimate sphere of these young women who are still maturing.

In many families, the mutations responsible for cancer risk are known (mainly *BRCA1/2*), giving to descendants one of two chances of having a mutation. In other families, no specific mutation can be diagnosed, and it is impossible to know for sure whether a family member carries a mutation. Such uncertainty makes communication with relatives or friends more complex, in particular when one tries to transmit oncogenetic information [3]. Consequently, a possible reaction to this incertitude may consist in denial, with a probable reduction of prevention efficacy.

Socioeconomic difficulties are a known cause of refusal of medical care [4]. This is also true for cancer prevention. Such difficulties represent an additional burden for some, although most medical care in France is cost-free for patients.

It is therefore very important to propose new strategies to communicate with young counselees in oncogenetics. We thus developed a psychoeducational intervention tailored for these young women and decided to test its efficacy in a prospective phase II trial. In this article, we describe the content of the intervention and the method to provide evidence of its interest.

## Methods

### Objectives

The main objective of this trial is to change the expectations and improve the coping of young women exposed to a high risk of hereditary breast and ovarian cancer (HBOC). Changes of expectations have been chosen as the first objective, while coping modifications have been placed within the secondary objectives. We expect that, given the type of information that will be provided during sessions, expectations may vary faster than coping manners, the former seeming more sensitive to information renewal.

Other secondary objectives are:To promote a better understanding of oncogenetic informationTo study if socioeducational differences may limit overall compliance with medical screening and if better social communication may help prevent refusal of careTo help these young women to build a more satisfying self-imageTo facilitate the way these young women resolve life issues such as marital relationships and procreation planning, and so to favor their emotional and sexual fulfillmentTo improve the chances of achieving a better long-term quality of life (QoL)To improve adherence to medical screening

### Psychoeducational intervention

The intervention will consist of a group session of a dozen participants at a spa center during a weekend. Participants will arrive on a Friday evening. After dinner, a television documentary about the story of a family with *BRCA* mutation will be shown. During the following 2 days, besides free spa activities available in the center, participants will attend ten small conferences lasting 15–30 minutes each. Experts will present the state of the art in various domains, including the following:Latest knowledge in oncogenetics (presented by an oncogeneticist possessing doctoral and medical degrees who is also an academic researcher in this domain)Recommendations and morbidity of prophylactic breast surgery and adnexectomy (presented by a surgeon specialist in gyneco-oncology)Psychological aspects in oncogenetics (presented by a clinician psychologist possessing a master of science degree)Epidemiology of HBOC and comparative mortality risks with other syndromes or life habits: how one can reduce cancer risk (e.g., tobacco, alcohol, breastfeeding) (presented by a statistician possessing a master of science degree)Good methods of breast cancer prevention (presented by a medical doctor who is a clinician senologist responsible for breast cancer screening)Assisted medical procreation and embryo selection (presented by a clinician possessing medical and doctoral degrees and specializing in this domain)Importance of nutrition and physical activity as risk modulators (presented by an academic researcher possessing medical and doctoral degrees and a nutritionist)Description of the assistance program developed to help counselees exposed to a high cancer risk (HBOC, Lynch syndrome) following their medical screening (presented by an oncogenetic counselor as well as a clinical nurse specialist)Health insurance facilities and social financial support (presented by a professional social worker)

For 15 minutes after each conference, participants will be able to comment on what they heard and/or to ask questions of the experts.

The remaining time after this preliminary information (i.e., about a half of the weekend) will be devoted to group activities, in particular role-playing games (Moreno psychodrama approach [5]) and group sharing under the supervision of a psychotherapist. The psychodrama will start with a short presentation of the rules: general empathy, no acting, and no after-session talking or gossiping about what happened or what was said, in particular naming participants, as well as silence when a role-play is ongoing. The second step asks participants to volunteer and stage a particular concern or difficulty that they would like to “treat.” If several persons volunteer, an election is undertaken to select the topic appearing most important to the majority of participants. If no one volunteers, the process starts with a “sticker game” with a theme such as “what I think of your mutation.” Each participant has to write on a small paper a short sentence (corresponding to the theme) describing what she may feel about another participant and sticks it on the latter’s forehead. Once all labels are stuck, all participants sit back in a circle and, one after another, each unglues her sentence, reads it aloud, and comments on it. Depending on the emotions raised during this exercise, a theme will be chosen for the psychodrama and role-played by participants under the regulation or direction of the psychotherapist. The selected participant explains the situation she selected, including the protagonists, the details of the event, and the difficulties she faces, and then chooses another participant to play her role. The stage director organizes the replay, promotes dialogue, invites standing in, enriches the drama, sheds light on dark zones, and proposes alternatives. If the game happens to be short, another “drama” can be introduced and played. About 3 h will be devoted to this exercise and the group sharing just afterward, leaving some time for spa activities before dinner.

We expect that the greatest effect of our intervention on expectations and coping will rely on how participants integrate the delivered information and how the exercises enable them to objectivize difficulties and suggest possible solutions. Such an intervention, if it is to be generalized, would induce numerous costs: the weekend session in a spa center (2½ days), experts’ fees, transportation of participants and experts, psychologists’ time, and organization costs. Overall, these costs would represent about $600 per participant (excluding data management, study design, and analysis).

### Study design

The study is a randomized, prospective, monocenter, psychoeducational phase II trial comparing the evolution of indicators between preintervention and 6 months postintervention. Two groups will be compared: a first group of asymptomatic participants who will attend the session immediately and a second group corresponding to the “waiting list” (control group). The waiting list session will occur 6 months later than that for the first group. Measured indicators will be obtained 2 weeks before and 6 months after the first intervention for all participants, whatever their allocation group (Table 1). This will be possible because the questionnaires will be completed by participants at home on a dedicated website. Groups will therefore be comparable, and the only difference between them will be limited to the intervention.

**Table 1 Tab1:** Schedule of enrollment, interventions, and assessments

		Study period				
	Enrollment and allocation	Baseline values	Session 1	Main outcome values	Session 2	Secondary outcome values
Time points	April-May 2016	First week of June 2016	Third weekend of June 2016	First week of November 2016	Third weekend of November 2016	End of May 2017
Enrollment						
Answer to the invitation letter	X					
Consultation and informed consent	X					
Allocation to session 1 or 2	X					
Website learning	X					
Interventions						
Group session 1			X			
Group session 2					X	
Assessments						
Socioeconomic data	X					
Psychosocial questionnaires		X	X	X	X	X

In March 2016, the study was approved by the local ethics committee (CPP SUD-EST-6: IRB00008526) and registered with ClinicalTrials.gov (NCT02705924).

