### Randomization

Participants will be randomized 1:1 to the first or second session (intersession delay = 6 months) using a minimization technique and stratified according to the existence or absence of a familial *BRCA* mutation. We assumed that this characteristic might induce variations in coping and expectations and thus alter the impact of the psychoeducational intervention if the studied population were not balanced with regard to this characteristic.

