The lability of some psychosocial dimensions makes them useless to test the effect of an intervention. This was the case for Rustøen et al. [19] in their study of the impact of a psychoeducational intervention based on hope improvement in newly diagnosed cancer patients. It enabled them to significantly improve the Nowotny Hope Scale score after 2 weeks, but no gain was noticed after 6 months. Obviously, in these patients, if chemotherapy/radiotherapy is needed and/or if the surgery is ablative or handicapping, the consequences of the treatments nullify any benefit that might be gained using a short-term psychosocial intervention. Even without deleterious circumstances, short-term improvements that do not last are very frequent in our context. For example, a very strong postintervention decrease in Hospital Anxiety and Depression Scale [43] anxiety score was observed in another randomized trial testing a 2-week psychoeducational group intervention. That study addressed patients with breast cancer previously treated by adjuvant chemotherapy, and physical activity and nutrition were the main topics of the intervention [44]. This immediate improvement of anxiety measured after the intervention was followed by a return to basal values at 6 months, persisting for the long run. In the present study, our 6-month primary objective takes into account an assumed stability of expectations over such a delay in the absence of intervention and a persistence of the improvement due to the session—if any—lasting at least 6 months. In our context, if improvement of scores would last for a shorter time, the intervention would be of low interest. The 1-year evaluation constitutes a secondary endpoint that will enable us to verify whether the 6-month results are maintained.

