### Trial status

The trial was not started when this article was written (October 18^th^, 2016).

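### The text times the primary assessment 6 months after session 1, but Table 1 places it at about 4.5 months; the two must be reconciled before any claim of 6-month persistence

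*Protocol article*

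**What the plan says.** The protocol article gives the timing of the primary assessment in words and in a calendar.

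- **Text, Study design:** "Measured indicators will be obtained 2 weeks before and 6 months after the first intervention for all participants, whatever their allocation group". The same section adds "The waiting list session will occur 6 months later than that for the first group", and the Randomization section repeats "intersession delay = 6 months".
- **Calendar, Table 1:** baseline "First week of June 2016", session 1 "Third weekend of June 2016", main outcome "First week of November 2016", session 2 on the third weekend of November 2016, and a last assessment at the end of May 2017.
- **Clock origin:** the Sample size and Data analysis sections count the 6 months from inclusion. The Discussion says the baseline questionnaire was moved from inclusion to a fixed date two weeks before session 1, because otherwise the 6-month delay would not hold for women enrolled early.
- **Hypothesis:** the Herth Hope Index section names persistence for 6 months or more as the main endpoint. The Discussion says that "if improvement of scores would last for a shorter time, the intervention would be of low interest".
- **Status:** "The trial was not started when this article was written", with the date 18 October 2016.

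**The concern.** The primary endpoint is about duration as much as size: hope should still be raised 6 months after the weekend. The Discussion explains why that delay was chosen. It cites a trial in newly diagnosed cancer patients in which a gain in hope at 2 weeks was gone at 6 months, and another in which an early fall in anxiety had returned to its starting level by 6 months. Decay within the first 6 months is therefore the authors' own worry.

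The table that is meant to implement the 6-month rule stops the controlled observation well short of it. If its spacing were carried into the live trial, a positive result would be reported as 6-month persistence although no controlled measurement had been made at that time. That result would then feed the larger phase III trial that the Discussion foresees.

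**Working it through.** **Inputs.** All dates are from Table 1. By the 2016 calendar, the third weekend of June is 18–19 June and the third weekend of November is 19–20 November. Participants arrive on the Friday evening (Psychoeducational intervention section), so session 1 starts on 17 June and session 2 on 18 November. First weeks are taken as days 1 to 7. One month = 365.25/12 = 30.44 days.

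**Does the calendar reproduce the text?** The baseline does: 1–7 June is 10 to 16 days before 17 June, which fits two weeks. The 6-month figures do not:

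| Interval | Text | Dates used | Days | Months |
|---|---|---|---|---|
| End of session 1 to main outcome | 6 months | 19 June to 1–7 Nov | 135–141 | 4.4–4.6 |
| Start of session 1 to main outcome | 6 months | 17 June to 1–7 Nov | 137–143 | 4.5–4.7 |
| Session 1 to session 2 | 6 months | 18 June to 19 Nov | 154 | 5.1 |
| Baseline to main outcome | – | 1–7 June to 1–7 Nov | 147–159 | 4.8–5.2 |
| Inclusion to main outcome | 6 months | 1 April–31 May to 1–7 Nov | 154–220 | 5.1–7.2 |

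Only a clock started at inclusion can reach 6 months, and then only for some participants.

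**Shortfall.** Six months from 19 June is 19 December, which is 183 days. 183 − 141 = 42 and 183 − 135 = 48, so the assessment is 6 to 7 weeks early. 42/183 = 23% and 48/183 = 26%, so about a quarter of the intended window is unobserved.

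**Can a later wave fill the gap?** From 19 June 2016 to 31 May 2017 is 346 days (11.4 months after session 1). From 20 November 2016 to 31 May 2017 is 192 days (6.3 months after session 2). By then both arms have attended, so this wave has no untreated control and gives only before–after information.

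**Can the assessment alone be moved?** 19 December is 30 days after 19 November. At 6 months the waiting-list arm would already have had its session, so session 2 has to move too.

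**Possible overstatement.** The article gives no decay curve, so this is an assumption. If the effect falls linearly from its peak at the session to zero at T months, the effect at t is proportional to 1 − t/T, and the ratio of the 4.5-month to the 6-month effect is (T − 4.5)/(T − 6):

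- T = 12: 7.5/6 = 1.25
- T = 9: 4.5/3 = 1.5
- T = 7: 2.5/1 = 2.5
- no decay: 1.0

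**The case against.** The strongest reply is that 6 months is the stated rule throughout the text and only the calendar departs from it. The Trial status section says nothing had begun by 18 October 2016, after the table's dates for enrolment, baseline and session 1. The table therefore looks outdated and is no evidence of a decision to measure at 4.5 months. This stands. A reader might infer that the trial can never support its 6-month claim; the article supports that only if the table's spacing is carried forward.

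A second reply is that the clock may run from inclusion or from baseline. From baseline the shortfall is about 1 month instead of about 1.5, and from inclusion it can vanish. But the Study design section counts from the intervention, the Discussion moved baseline away from inclusion, and persistence means time since the session. The reply shows that the clock origin is itself unclear; it does not remove the contradiction.

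Three further inferences go too far.

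- **A biased comparison.** Both arms are measured on the same dates and before session 2, so the contrast at about 4.5 months is a fair randomised one.
- **A fixed inflation factor.** Any single ratio rests on an assumed decay. Under the authors' own hypothesis of a lasting effect there is no inflation.
- **A faulty final wave.** It reads the arms at 11.4 and 6.3 months after their sessions, but the article plans no replication of session 1 by session 2. Any common last wave in a waiting-list design has unequal delays.

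**Conclusion.** The text and Table 1 contradict each other on when the primary endpoint is measured (6 months against 4.4–4.6 months after session 1) and on the gap between sessions (6 against 5.1 months). No clock started at the session or at baseline gives 6 months.

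If the table's spacing is kept, the trial validly estimates the effect at about 4.5 months; what fails is the 6-month label and the persistence conclusion. The size of any overstatement cannot be known from the article: nil without decay, and 1.25 to 2.5 times for linear decay to zero between 12 and 7 months. The conclusion rests on calendar arithmetic and on the spacing being followed; it needs no decay assumption. Because it concerns the timing of the primary endpoint, it should be settled before baseline data are collected.

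**What to change.** Reconcile the text and Table 1 when the calendar is re-dated. Two consistent solutions exist, and the choice is the sponsor's.

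1. **Keep the 6-month endpoint.** Schedule the main questionnaires 6 months after session 1 and session 2 after them. The questionnaires are completed online at home, so they cost nothing extra. The real cost is that session 2, a residential weekend with invited experts, moves later relative to session 1: by about 4 weeks to clear the 6-month date (30 days), or about 6 weeks if the present gap of 11 to 17 days between questionnaires and session 2 is kept (41 to 47 days). The stated delay between sessions must be amended to match.
2. **Keep the spacing.** Restate the primary endpoint as about 4.5 months after the session throughout, correct the stated delay between sessions to about 5 months, and drop the 6-month persistence claim. This costs only wording, but the trial then no longer tests the duration that the authors regard as worthwhile.

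In either case, name one clock origin, session 1 or the fixed baseline, and use it in the Sample size and Data analysis sections in place of inclusion.

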### Population

Participants must belong to HBOC families, be aged between 18 and 30 years, be single, and be childless without any personal history of cancer. They must have consulted at the oncogenetics department of the Jean Perrin comprehensive cancer center (CCC) and must been tested for the presence of germline *BRCA* mutations. If a familial germline *BRCA* mutation has already been diagnosed, these women must carry the familial mutation. If no known deleterious mutation has yet been found within the family, these women may be included if their familial risk is high (Eisinger score ≥6 or Manchester score ≥16) [6–8]. To limit travel costs, participants must live in the Auvergne region (central France). Participants must also sign an informed consent form before inclusion.

Exclusion criteria include pregnant women and those who cannot answer questionnaires either because of language difficulties or because they cannot write in French correctly. Counselees who cannot connect to the dedicated website will also be excluded, but this is not likely to happen. Psychiatric disorders and/or ongoing related treatments will also result in exclusion, as will any treatment incompatible with a 2-day stay in a spa center.

